### Data collection, management and analysis

#### Study conduct

Study nurses will be trained to conduct the data collection at the five designated primary health clinics in Seremban district. At the baseline assessment, the principles of the trial will be explained again for the subject and spouse and they will be asked to provide consent by signing the consent form. One original copy of each form will be kept by the study nurse who will file the document on site. One copy of each form will be given to the subjects. The women and their spouses will have linked ID numbers by assigning each subject and spouse the same ID number with subject ID ending with the number ‘2’ and spouse ID ending with the number ‘1’ respectively.

#### Data collection

At baseline the subjects will undergo measurements of waist circumference, hip circumference, weight, height and blood pressure by following standardised procedures based on World Health Organisation (WHO) STEPS surveillance [32]. Only the subject in the couple will provide a 10-mL blood sample to measure glycated haemoglobin A_1c_ (HbA_1c_) and a fasting lipid profile (triglycerides (TG), low-density lipoprotein cholesterol (LDL-C), high-density lipoprotein cholesterol (HDL-C) and total cholesterol (TC)). Due to the need for a fasting lipid profile analysis, the subject will be asked to come to the clinic after fasting for a minimum of 9 h. In line with this, the data collection time-points are planned to be in the morning. The European Health Literacy Tool Q-47 (HL-EU-Q47) [33] (HL-EU Consortium 2012), the Malaysian Food Frequency Questionnaire (FFQ), modified to be used in the current trial [2]; the International Physical Activity Questionnaire (IPAQ) [2]; and the Depression Anxiety Stress Scale 21-items (DASS-21) [34, 35] will be used to collect data on level of health literacy, dietary pattern, physical activity level, and stress level, respectively. Data such as socio-demographic parameters and family history of diabetes will be collected by structured interviews with the study nurse. The spouse will undergo the same data measurements, with the exception of blood sampling. At the end of the data collection, and before subject and spouse leave, data will be checked by the study nurse and site coordinator or research officer, to ensure that all data forms and questionnaires have been filled correctly. When data collection is completed the data collection forms and questionnaires will be signed-off by the study nurse and site coordinator or research officer. At the end of the baseline visit, if the subject is randomised to the intervention, the first contact with a CHP will be made. The subject and spouse will be introduced to the mobile application and it will be installed on the subject’s and spouse’s smartphone device. If the subject and spouse have sufficient time the CHP will proceed with the first contact point. If the subject and spouse do not have the time, an appointment will be set in the next 5 days either at the clinic or at the couple’s house. The same measurements, except height, socio-demographic parameters and medical history, described above will be conducted at the endpoint visit (Table 2).

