**Method/design:**

Eligible subjects will be Malaysian women in the age group 20 to 39 years, who are nulliparous, not diagnosed with diabetes and own a smartphone. With an alpha-value of 0.05, a statistical power of 90 %, 264 subjects will need to complete the study. Subjects with their spouses will be randomised to either the intervention or the control arm for an 8-month period. The primary endpoint is change in waist circumference from baseline to end of intervention period and secondary endpoints are changes in anthropometric parameters, biochemical parameters, change in health literacy level, dietary habits, physical activity and stress level. Primary endpoint and the continuous secondary endpoints will be analysed in a linear regression model, whereas secondary endpoints on an ordinal scale will be analysed by using the chi-squared test. A multivariate linear model for the primary endpoint will be undertaken to account for potential confounders. This study has been approved by the Medical Research and Ethics Committee of the Ministry of Health Malaysia (protocol number: NMRR-14-904-21963) on 21 September 2015.

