### Study design

The trial is designed as an unblinded, RCT to assess the efficacy of a complex behavioural change intervention aiming to improve the overall health of young women prior to their first pregnancy. The intervention follow-up period is 8 months from randomisation/baseline. After end trial the subjects will be monitored for a period of 12 months for pregnancy. Figure 1 gives the flow diagram of the trial. The trial was designed following the Standard Protocol Items: Recommendations for Interventional Trials (SPIRIT) 2013 statement (see Additional file 1).

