#### Randomisation

At the baseline measurement visit, subjects will be randomised into the intervention and control arms at a 1:1 allocation ratio. Random allocation sequences will be computer- generated with block sizes of six subjects. Each clinic will be provided with a sufficient number of identification (ID) numbers with randomisation codes. When a subject is enrolled in the trial, the study nurse should assign the lowest available ID number to the subject from the list of ID numbers.

The Institute for Health System Research (IHSR) under the MoH has prepared the randomisation list and these are distributed to the five designated primary health clinics in Seremban. A copy is maintained by the IHSR.

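### As written, nothing masks the month-8 waist measurement, so the primary endpoint is open to observer expectation

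*Protocol article*

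**What the plan says.** The abstract fixes the outcome: "The primary endpoint is change in waist circumference from baseline to end of intervention period". Under Study design: "The trial is designed as an unblinded, RCT to assess the efficacy of a complex behavioural change intervention". No qualification follows about who is or is not masked.

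The staff roles are set out in three places.

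- Randomisation: "Each clinic will be provided with a sufficient number of identification (ID) numbers with randomisation codes". At enrolment, "the study nurse should assign the lowest available ID number to the subject from the list of ID numbers".
- Study conduct: "Study nurses will be trained to conduct the data collection at the five designated primary health clinics in Seremban district".
- Data collection, on the baseline visit: "At the end of the baseline visit, if the subject is randomised to the intervention, the first contact with a CHP will be made". For month 8: "The same measurements, except height, socio-demographic parameters and medical history, described above will be conducted at the endpoint visit (Table 2".

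The measurements are to be made "by following standardised procedures based on World Health Organisation (WHO) STEPS surveillance". According to Intervention, the behavioural programme is delivered by CHPs, a role separate from the study nurses.

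**The concern.** Couples and CHPs cannot be masked to counselling and an app. The person holding the tape at month 8 can be, and the article gives no reason for leaving her unmasked. The group of nurses that allocates women from coded lists is also the group trained to collect the data, and CHP contact begins at the end of the baseline visit in one arm only. The arm is therefore easy to know at the clinic.

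A waist reading depends on tape position, tension and the phase of breathing. A small systematic difference between arms in how it is taken would look exactly like benefit. It would also pass into the waist-to-height and waist-to-hip ratios, which use the same reading and so cannot corroborate it independently. Adjusting for baseline waist, as Statistical analysis plans, does not remove a differential error that arises at month 8.

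This is detection bias at the endpoint visit. It is a different matter from predictability of the allocation sequence, and concealing the sequence would not cure it.

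**Working it through.** **Inputs from Sample size calculation:** difference 2 cm, SD 5 cm, two-sided alpha 0.05, power 90%, 132 women per arm. **Assumed, because the article gives no value:** a differential reading error b favouring the intervention, ranged over 0.25, 0.5 and 1.0 cm.

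1. *The plan's own figure.* n per arm = 2 × (1.960 + 1.282)² × 5² / 2² = 12.5 × 10.51 = 131.3, rounded up to 132. The exact t test gives 132.3 per arm, and power 0.899 with 132. The stated 132 reproduces.

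2. *Standard error of the arm difference.* SE = 5 × √(2/132) = 0.615 cm. The smallest observed difference that reaches significance is 1.960 × 0.615 = 1.21 cm.

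3. *False-positive rate with no true effect and error b.* P = P(Z > 1.960 − b/SE) + P(Z < −1.960 − b/SE).

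| b (cm) | Share of 2 cm | b/SE | Upper tail | Lower tail | Total |
|---|---|---|---|---|---|
| 0 | 0% | 0 | 0.025 | 0.025 | 5.0% |
| 0.25 | 12.5% | 0.406 | 0.0601 | 0.0090 | 6.9% |
| 0.5 | 25% | 0.812 | 0.1256 | 0.0028 | 12.8% |
| 1.0 | 50% | 1.625 | 0.3688 | 0.0002 | 36.9% |

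4. *Do the stated safeguards hide the arm?* Nurse training and STEPS procedures standardise the reading. Checking and sign-off of forms, double data entry and independent monitoring address completeness, transcription and adherence. None of them conceals the arm from the measurer or would detect a tape held slightly tighter in one arm.

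**The case against.** The strongest reply is that the article never says who measures at month 8. The endpoint sentence is passive, the nurse in Randomisation acts at enrolment, and Study conduct speaks of nurses in the plural across five clinics. The article condenses a full protocol (version 4.0) and refers to a SPIRIT file, neither of which is shown, and endpoint staffing may be settled there. The nurses are trained, the procedure is standardised, and on the text they do not deliver the intervention, which weakens the motive for bias. Every value of b is assumed.

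Much of this stands, and it limits what can be claimed. Three stronger readings are tempting:

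- *The month-8 measurer knows the arm, or is the nurse who allocated that woman.* No sentence says so. It is inferred from an unqualified unblinded design, codes held at the clinic and one staff group for both tasks.
- *The measurer has the baseline waist in front of her.* This is not shown. Under Data management the original completed forms go to the Institute for Health System Research (IHSR), and no retained clinic copy of the measurements is described.
- *The trial's result will be biased by a particular amount.* The documents give no basis for any value of b. An error of 1.0 cm is half the target effect and goes well beyond a few millimetres.

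The reply does not dispose of the point. The article does more than stay silent: it declares the trial unblinded and assigns the roles step by step, and following those steps leaves the primary measurement unprotected. Standardisation and separate delivery of the intervention lower the risk without removing it.

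**Conclusion.** The point holds as a design weakness that should be corrected. Followed as written, the plan permits the month-8 waist to be taken by a nurse who knows the arm; that she does know it is a strong inference and not a stated fact.

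The plausible scale is a false-positive rate of about 7 to 13% in place of 5%, for an assumed differential error of 0.25 to 0.5 cm. The figure of about 37% at 1.0 cm marks an extreme. These results rest on the plan's SD of 5 cm, 132 completers per arm, a normal approximation, no true effect, and an error in the intervention's favour. The sample size itself is not in question. HbA1c and lipids are laboratory measures and are less exposed.

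**What to change.** Mask the endpoint waist and hip measurements, using existing staff.

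- Keep the allocation list away from the endpoint measurer, held by the site coordinator or centrally at IHSR. The research officer should not hold it: that role recruits couples (Screening) and may sign off the data forms (Data collection). Since the site coordinator may also sign off forms, a coordinator who holds the list should leave the endpoint sign-off to someone else.
- Where staffing allows, have the reading taken by a study nurse who did not allocate that woman.
- Take waist and hip first, before the questionnaires and before any talk about the app or the CHP.
- Use an endpoint form that shows neither the arm nor the baseline waist, with IDs that do not reveal the arm. Omitting the baseline value is a precaution.
- Ask women not to disclose their arm.
- Describe the trial as open-label with an assessor-masked primary endpoint. If masking is already practised, stating this is the only change needed.

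The cost is some scheduling effort, some between-observer variation in the change score if a different nurse measures, and some accidental unblinding by participants. Sample size, endpoint and allocation ratio are unchanged. The change can apply to every endpoint visit not yet held, even though recruitment has begun.

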**Table 2 Tab2:**
[figure not shown]
Data collection at each time-point in the Jom Mama trial

Data collection on woman;● Data collection on spouse; ^a^
*FFQ* Food Frequency Questionnaire, ^b^
*IPAQ* International Physical Activity Questionnaire, ^c^
*DASS*-*21* Depression Anxiety and Stress Scale 21-items, ^d^ Fasting lipid profile: will be measured as a combination of: total cholesterol (TC) level, low-density lipoprotein cholesterol (LDL-C) level, high-density lipoprotein cholesterol (HDL-C) level and triglyceride (TG) level; 
^5^Exit point visit will occur if the woman becomes pregnant between 4.1 months and 8 months after randomisation

If a subject becomes pregnant within the 8-month intervention period, she will be withdrawn from the trial. Exit measurements, which are similar to those at the endpoint visit, will be performed only for subjects who become pregnant between 4.1 and 8 months from baseline. For those who become pregnant between baseline and month 4 in the intervention period, no measurements will be taken.

#### Data management

All data will be managed and stored with protection of data privacy. Documentation as well as corrections, if necessary, will be done in accordance to Good Clinical Practice guidelines. All protocol-required information collected during the trial must be entered on a data collection form containing the four questionnaires. The original completed data collection form will be send to IHSR, MoH Malaysia, where double data entry will be performed by two independent data clerks. The completeness, validity and plausibility of data are examined by validating programmes, which thereby generate queries. The generated queries will be checked with original data collection forms and all changes from the original data are documented on audit files. Data will be maintained and analysed in the statistical Stata programme, version 12.0 or higher (StataCorp LP). Monitoring will be performed regularly by an independent clinical research organisation from Malaysia to check the completeness of the contents of records and the data collection forms, the adherence to the protocol and the progress of enrolment.

#### Statistical analysis

The null hypothesis is that there is no difference in the change in waist circumference between the intervention and the control group after the 8-month intervention. The alternative hypothesis is that the decrement in waist circumference will be bigger in the intervention group compared to the control group after the 8-month intervention. A linear regression model will be used to assess the difference in the change of waist circumference from baseline to end of intervention, with the difference in waist circumference as the independent variable, treatment (intervention versus control) and baseline waist circumference as covariates. Additional tests will be performed for the impact of the intervention in both high- (waist circumference above 80 cm) and low-risk (waist circumference below 80 cm) groups. This will be done by subgroup analysis or by assessing the proportional changes in the primary endpoint. Each subgroup will also be analysed in a linear regression model. The continuous secondary endpoints will be analysed in a linear regression model, whereas the difference in the change of each secondary endpoint from baseline to end of intervention, will be the dependent variable, treatment (intervention versus control) and baseline value as covariate. Regarding health literacy (HL-EU-Q47), physical activity (IPAQ) and stress (DASS-21) all the variables are ordinal and, therefore, independence between intervention and control groups will be tested with the chi-squared test. Change in nutrient intakes will be compared between the groups using a generalised linear model, with additional adjustments for total energy intake. Nutrient and food patterns before and after the intervention will be explored in both groups separately by using dimension reduction techniques such as principal component analysis. Multivariate analysis will be performed to assess the association between exposure to the intervention, primary endpoints and secondary endpoints (BMI, waist-to-height and waist-to-hip ratio, HbA_1c_, lipid profile, blood pressure, health literacy, physical activity, dietary intake and stress level) using linear regressions. In this model the secondary endpoint will be included in the model as covariates and the estimated coefficients will be presented unadjusted and adjusted for appropriate and/or effect modifier and/or confounders. Furthermore, interactions between the secondary endpoints will also be explored. Several supportive analyses will be performed. The first supportive analysis will explore the relation between subjects’ and spouses’ change in waist circumference and other anthropometric measurements, diet, physical activity, health literacy and stress. A second supportive analysis will explore whether a short intervention period (subjects who become pregnant between 4.1 and 8 months in the intervention period), will also have an impact on the primary endpoint and secondary endpoints. A time variable explaining how long they have been included in the intervention will be included in the models as a covariate. At the end of the 12-month post-intervention monitoring period, a full analysis will be conducted on subjects who become pregnant within 12 months after completing the intervention. This will be done by assessing the incidences of GDM among women who became pregnant between treatment groups, using a chi-squared test. Additionally, a logistic regression model to explore associations between the number of subjects with GDM and several secondary endpoints will be conducted.

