### Intervention

The intervention has two components. The first component is an interaction with a CHP who will be in contact with the women and their spouses during the 8-month intervention period. These contacts will be a combination of three face-to-face meetings, three phone calls and communication through Whatsapp group chat. The CHP will use motivational counselling techniques, i.e. motivational interviewing, to support and motivate the young women and their spouses to live a healthier lifestyle. The second component is an E-health platform which consists of two elements: (1) a mobile application in the form of a habit formation application, where subjects and spouses can select different challenges for obtaining a healthy diet, more physical activity and less sedentary behaviour during the intervention period; and (2) a web-based back-end interface which can be accessed by the CHP, which will be her tool to assess the women and their spouses’ lifestyle situation. The CHP uses a dashboard to follow the progress of subject and spouse in performing the challenges, and uses the information to interact with the subject and her spouse during the contact points in the intervention. Figure 2 presents screen shots of the web-based application the CHPs are using. The CHP will function as a personal coach to engage, support and guide the young woman and her spouse toward achieving and maintaining a healthier lifestyle. During the interaction over the intervention period of 8 months, the CHPs will assess the subject and her spouse’s health risks and behaviour, share information on healthy living and support the subjects and spouses to reach their personal health goals. The objectives of each contact point are presented in Table 1.

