**Fig. 2 Fig2:**
[figure not shown]
Screen shot from the web application, showing the couples’ dashboard. Screen shot **a** Shows the overview of all couples under one community health promoter (CHP). The traffic lights give an indication on how active the couple are in performing their selected challenges. The *second column* indicates when the couple was last active on the mobile application. The *last column* informs when the CHP has the next appointment with the couple. Screen shot **b** Shows the progress over time for one couple. The graphic can shift between wife and husband and, in this example, it is only showing the wife. The *upper columns* indicate how many times the challenges have been performed per month. The *lower columns* indicate how many times each challenge has been performed

**Table 1 Tab1:** Overview of the objective of each face-to-face and phone call contact point

Contact point	Objective
Contact point 1 (face-to-face)	Assessment of woman and spouse’s health risk and behaviour: conversation starter
	Introduce to use of mobile application
	Initiate review of assessments and behaviour change process
	Goal setting
Contact point 2 (face-to-face)	Follow-up on use of mobile application
	Provide health information as required
	Review and address extrinsic supportive and inhibiting factors
	Introduce proactive coping
Contact point 3 (phone)	Follow-up on use of mobile application
	Follow-up on progress based on initial goal setting
	Provide support and advice
	Provide health information as required
	Revise goal setting and set new goals as relevant
Contact point 4 (phone)	Follow-up on use of mobile application
	Follow-up on progress based on previously set goals
	Provide support and advice
	Provide health information as required
	Revise goal setting and set new goals as relevant
Contact point 5 (face-to-face)	Follow-up on use of mobile application
	Follow-up on progress based on previously set goals
	Provide support and advice
	Provide health information as required
	Revise goal setting and set new goals as relevant
Contact point 6 (phone)	Follow-up on progress based on previously set goals
	Provide support and advice
	Provide health information as required
	Goal setting and planning for the future
	End of intervention process

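### The primary regression omits clinic, within which allocation appears to be blocked, and neither it nor the power statement allows for women sharing a community health promoter in one arm

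*Protocol article*

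**What the plan says.** In the protocol article, Statistical analysis, the primary analysis is a linear regression of the change in waist circumference, with "treatment (intervention versus control) and baseline waist circumference as covariates". No clinic term, CHP term, random effect or robust variance is named.

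Under Randomisation, women are "randomised into the intervention and control arms at a 1:1 allocation ratio". The section continues: "Random allocation sequences will be computer- generated with block sizes of six subjects". On the lists it says that "these are distributed to the five designated primary health clinics in Seremban", and also: "Each clinic will be provided with a sufficient number of identification (ID) numbers with randomisation codes". The study nurse takes the lowest unused number. The word stratified does not appear.

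Under Intervention, each couple has three meetings and three calls with a CHP, plus "communication through Whatsapp group chat". The legend of Fig. 2 describes a dashboard screen: "Shows the overview of all couples under one community health promoter (CHP". Under Control arm, controls have no contact with a CHP.

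Under Sample size calculation, a two-sided t test with a 2 cm difference, SD 5 cm, alpha 0.05 and 90 % power gives 132 women per arm. There is no design effect. The number of CHPs, their caseload and an intraclass correlation (ICC) are not given.

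**The concern.** There are two separate mismatches between design and analysis.

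**Clinic.** If every clinic works through its own blocks of six, each clinic contributes nearly equal numbers to both arms. Differences between clinics in waist change (staff, measurement, case-mix) then largely cancel from the treatment contrast. A model without clinic still counts them as residual noise, so its standard error is larger than the design warrants.

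**CHP.** Women coached by the same CHP share that person's skill and style. Any resulting correlation exists in the intervention arm only. Ordinary regression ignores it, so the standard error is too small if CHPs differ in effect, and the 90 % power rests on an independence assumption that is not stated.

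At stake are the width of the primary confidence interval, the actual error rate of the primary test, and the meaning of the power figure.

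**Working it through.** **1. The plan's own figure.** n per arm = 2 × (1.960 + 1.282)² × 5² / 2² = 131.3, rounded up to 132, with power 0.901. The exact t test gives power 0.899 at 132. The stated figure therefore reproduces, under independent women.

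**2. Clinic omitted.** Let s be the share of the variance of waist change due to clinic (assumed; not in the article), with arms balanced within clinic.
- Model SE / true SE = 1/√(1 − s)
- Actual two-sided error = 2 × [1 − Φ(1.96/√(1 − s))]

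| s | SE ratio | Two-sided error |
|---|---|---|
| 0.01 | 1.005 | 0.049 |
| 0.02 | 1.010 | 0.048 |
| 0.05 | 1.026 | 0.044 |
| 0.10 | 1.054 | 0.039 |

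**3. CHP omitted.** Let k be the number of CHPs and m = 132/k the analysed women per CHP. Both k and the ICC are assumed.
- Design effect, intervention arm only: DE = 1 + (m − 1) × ICC
- Model SE = 5 × √(2/132); true SE = 5 × √((1 + DE)/132)
- Actual error = 2 × [1 − Φ(1.96 × model SE / true SE)]
- Power with the correct SE = Φ(2/true SE − 1.96)

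Middle case, k = 10 and ICC = 0.02: m = 13.2; DE = 1 + 12.2 × 0.02 = 1.244; true SE = 5 × √(2.244/132) = 0.652; SE ratio = √(2.244/2) = 1.059; error 0.064; power Φ(3.07 − 1.96) = 0.87.

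| CHPs | ICC | DE | SE ratio | Error | Power |
|---|---|---|---|---|---|
| 20 | 0.01 | 1.06 | 1.014 | 0.053 | 0.89 |
| 20 | 0.05 | 1.28 | 1.068 | 0.066 | 0.86 |
| 10 | 0.02 | 1.24 | 1.059 | 0.064 | 0.87 |
| 10 | 0.05 | 1.61 | 1.142 | 0.086 | 0.81 |
| 5 | 0.01 | 1.25 | 1.062 | 0.065 | 0.865 |
| 5 | 0.05 | 2.27 | 1.279 | 0.125 | 0.72 |

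**4. Simulation check.** Blocks of six in five clinics, 132 per arm, CHPs working within clinics, 4,000 runs per scenario, no average treatment effect.

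| Scenario | Error, stated model | Error, clinic added |
|---|---|---|
| No clinic or CHP effect | 0.047 | 0.047 |
| Clinic share 10 % | 0.042 | 0.051 |
| 10 CHPs, ICC 0.02 | 0.064 | 0.065 |
| 10 CHPs, ICC 0.05 | 0.089 | 0.091 |
| 5 CHPs, ICC 0.05 | 0.126 | 0.127 |
| 10 CHPs, ICC 0.05, and clinic share 5 % | 0.085 | 0.093 |

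Adding clinic restores the error rate where only clinic varies. It does not remove the CHP inflation. The last row shows the two effects pulling against each other.

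**The case against.** - **Blocking within clinic is inferred.** The article never says that randomisation is stratified. The inference from lists held at each clinic and used in order is reasonable, but it remains an inference.
- **The clinic effect is small and on the safe side.** The outcome is a change adjusted for baseline, so lasting clinic differences in waist are largely removed already. This stands. The case for clinic is efficiency and consistency with the design, and there is no added false-positive risk.
- **The size of the CHP effect is assumed.** A dashboard legend shows that one CHP follows several couples, but gives no number. With many CHPs and a low ICC the effect is minor. This stands.
- **The error-rate inflation depends on the null.** If the intervention changed no woman's outcome, CHPs could not create correlation through treatment. The inflation arises when CHP effects are non-zero but average to zero and CHPs are seen as a random sample. For inference about the particular CHPs used, ordinary regression is defensible. This stands, and it argues against replacing the primary model.
- **The article is condensed.** It cites a full protocol, version 4.0, which may contain more. But it names the covariates of the primary model and the sample-size method, so those can be reviewed as written. It cannot be concluded that no CHP sensitivity analysis exists elsewhere.

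Three stronger readings are tempting and are not supported. A reader might put power as low as 64 % and error at 16 %; at 132 per arm this needs 40 women per CHP, or 132/40 = 3.3 CHPs across five clinics. An error of 0.162 does arise with 198 per arm, five CHPs and ICC 0.05, but power there is 0.81. A reader might take the group chat as proof that couples influence each other, but the article does not say who is in a group. A reader might also conclude that the confidence interval must be wrong either way. Because the omissions act in opposite directions, they may partly offset each other.

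**Conclusion.** The point holds with limits. Leaving out clinic does not match the apparent randomisation groups and costs a little precision: an SE about 0.5–5 % too large and a two-sided error of about 0.049–0.039, if clinic explains 1–10 % of the variance and balance within clinic carries over to the women analysed.

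The CHP structure is real: shared coaches in one arm, none in the other, and a sample size without any allowance. Its size is a range only, on the assumptions set out above; the middle case is an error of 0.064 and power of 0.87. The net direction of the two omissions cannot be determined from the article. The documents do not support calling the planned test invalid, nor requiring a partially nested model as the primary analysis.

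**What to change.** 1. **Clinic.** Add clinic as a fixed effect to the primary model and to the linear models for the continuous secondary endpoints and the waist-circumference subgroups. The chi-squared comparisons of the ordinal endpoints are not affected. Cost: four degrees of freedom (with 264 women, residual degrees of freedom fall from 264 − 3 = 261 to 257).
2. **CHP.** Carry the CHP identifier into the analysis dataset; the dashboard implies that it exists. Name a sensitivity analysis of the primary endpoint with a random CHP effect in the intervention arm only and small-sample degrees of freedom.
3. **Power statement.** Say that 90 % power at 132 per arm assumes no clustering by CHP. Giving the planned number of CHPs would let readers judge how far this matters.

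The downside of step 2 is a wider interval in that analysis (about 1–28 % in SE over the assumed range) and an imprecise CHP variance if CHPs are few. If CHPs are tied to clinics, the CHP term will also overlap with any clinic-by-treatment difference, which should be noted when it is interpreted. Conduct and recruitment do not change.
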